## Abstract

**Introduction:**

Penicillin allergy labels (PALs) are reported in 1 in 10 hospitalised patients globally and associated with inferior patient, hospital and microbiological outcomes; however, the majority are incorrect and should be removed. Direct oral penicillin challenge has been demonstrated to be a safe and effective method for the removal of PALs. However, the question of whether a single dose is sufficient to ascertain true allergy status remains unanswered, with some studies suggesting that extended challenges of 3 or more days are superior for the exclusion of delayed immune reactions. The aim of the PROSPECTOR studies was to determine the feasibility (PROSPECTOR-1) of a definitive trial (PROSPECTOR-2) to evaluate the safety and effectiveness of prolonged oral challenge (ie, 5 days) versus single-dose oral challenge in patients with a delayed or unknown penicillin allergy phenotype (PROSPECTOR-2).

**Methods and analysis:**

A pair of double-blind two-arm parallel placebo-controlled trials will be undertaken**—PRO**longed versus **S**ingle dose in **PE**nicillin oral **C**hallenge **T**esting double-blind parallel group randomised placebo-c**O**ntrolled t**R**ial (PROSPECTOR Studies). Patients with a reported delayed or unknown timing penicillin allergy who have passed a supervised single-dose oral amoxicillin challenge (with or without prior skin testing/single or split dose) will be recruited. Informed patient consent will be granted for sites to recruit patients and collect routine clinical data. PROSPECTOR-1 will assess the safety and feasibility of a placebo-controlled trial for single-dose amoxicillin challenge versus 5-day prolonged oral challenge. PROSPECTOR-2 will assess the superiority of the 5-day prolonged oral challenge compared with single-dose amoxicillin challenge in excluding a delayed immune reaction. PROSPECTOR-2 will commence immediately post completion of PROSPECTOR-1 in a vanguard design, with adjustments to the projected sample size for superiority made following completion of PROSPECTOR-1. PROSPECTOR-2 will commence recruitment immediately following closure of PROSPECTOR-1; however, data from each trial will be analysed separately.

**Ethics and dissemination:**

These studies were reviewed and approved by the Austin Health Human Research Ethics Committee (PROSPECTOR-1: HREC/99740/Austin-2023 and PROSPECTOR-2: HREC/109785/Austin-2024). The results will be published in peer-reviewed journals and presented at relevant conferences.

**Trial registration number:**

PROSPECTOR-1: ACTRN12623001242617 and PROSPECTOR-2: ACTRN12624001107516.

STRENGTHS AND LIMITATIONS OF THIS STUDYThese studies are among the first double-blind randomised placebo-controlled trials in antibiotic allergy investigation.The pilot phase, randomised experimental design and recruitment of patients from existing inpatient or outpatient settings will minimise the opportunity for selection bias.The definitive trial is international and multicentre, allowing for increased sample heterogeneity and generalisability of results.The pilot study does not aim to explore the ideal number of days for prolonged challenge in eliciting true delayed allergy, so conclusions will be limited to comparison with a prolonged 5-day challenge, while there is still variability in practice globally.A two times a day 500 mg dose of penicillin is set as the intervention; however, variability in preferred dosage remains in prolonged challenge practice globally.

## Introduction

### Background and rationale

 Penicillin allergy labels (PALs) are commonly documented in patient electronic medical records (EMRs).^1^ At the higher end, the prevalence has been estimated at 10% for hospitalised Australians^2^ and 9.9% of inpatients in Montreal, Canada.^3^ A Danish study found that 5% of hospital inpatients carried a PAL,^4^ while at the lower end, the prevalence is estimated at 3.2% in hospital inpatients in South Africa^5^ and 2% for all beta-lactam allergy in Hong Kong patients.^6^ This figure may be even higher among vulnerable patients such as the immunocompromised,^7^ geriatric and rheumatology populations.^8 9^ Those patients who carry a PAL are more likely to receive an inappropriate antibiotic, suffer a hospital-associated adverse event and acquire a multidrug-resistant organism.^10^,^13^ PALs are also associated with increased hospital length of stay (LOS), higher readmission rates, increased hospital costs and mortality rates.^10 14 15^ At a public health level, they are associated with inappropriate prescribing and antimicrobial resistance.^1^

Despite their omnipresence, the majority of PALs are assessed as ‘low-risk’ and can be safely removed by penicillin allergy testing.^16^,^19^ Oral penicillin challenge with or without preceding skin testing is considered the gold standard for delabelling^20^; however, clinical equipoise remains regarding the superiority of single-dose or prolonged (ie, multiple-day dosing) oral challenge for patients who report a delayed or unknown timing penicillin allergy phenotype. The current Drug Allergy Practice Parameters recommend ‘against the routine use of multiple-day challenges in the evaluation of penicillin allergy’, providing a ‘strong recommendation’ but with ‘low certainty of evidence’.^21^ The European guidelines reviewed the literature of over 6484 patients, demonstrating a 2.3% positive rate following the initial challenge and 5.5% during the varied prolonged challenges. They concluded that there is no consensus on a preferred procedure and could not provide a recommendation for or against prolonged oral challenge.^22^

The results from a mixture of European observational and retrospective studies suggest that prolonged challenges ranging from 3 to 10 days may be superior to single-dose challenges at eliciting delayed immune reactions. However, the reported prevalence of delayed reactions is highly variable (5–12% of patients), and many were reliant on patient self-reporting.^23^,^30^ In a recent retrospective single-centre Danish study of 3179 low-risk patients, 2.6% were positive on day 1 of challenge and 7.2% after day 1.^31^ This contrasts with the North American experience, where prolonged challenges have been associated with low rates of delayed reactions (0–1.8%).^32^,^35^ A paediatric study demonstrated that delayed reactions may occur <7 days following a single challenge.^36^ This gap between guideline recommendations and evidence, and differing results across geographical regions, highlights the need for robust evidence to inform practice with clinical certainty.

Randomised controlled trials (RCTs) have not routinely been used to answer questions regarding best practice in penicillin allergy research, despite their ability to provide high-quality evidence. The PROSPECTOR (**PRO**longed versus **S**ingle dose in **PE**nicillin oral **C**hallenge **T**esting double-blind parallel-group randomised placebo-c**O**ntrolled t**R**ial) studies will use a double-blind, parallel-group, placebo-controlled RCT study design. PROSPECTOR-1 is an external pilot trial, which will assess the feasibility of conducting a blinded placebo-controlled trial of single-dose versus prolonged dose oral challenge in patients with a documented or reported PAL. It will also inform the sample size of a definitive full-scale trial, which will follow directly on from PROSPECTOR-1, with adjustments made as required based on effectiveness and feasibility outcome data. PROSPECTOR-2 is the definitive trial, which will assess whether a prolonged oral challenge is superior to a single dose challenge for ascertaining true immune-mediated penicillin allergy.

### Objectives

PROSPECTOR-1: To evaluate the feasibility of a placebo-controlled trial and inform the design of a definitive trial evaluating whether prolonged oral challenge (5 days) is superior to single-dose oral challenge in patients reporting penicillin allergy with delayed or unknown timing phenotype to ascertain a true immune-mediated adverse reaction. PROSPECTOR-2: To evaluate the effectiveness of prolonged oral penicillin challenge (5 days) over single-dose penicillin challenge for ascertainment of true penicillin allergy (ie, immune-mediated allergy).

### Trial design

The PROSPECTOR studies are multicentre, prospective, double-blinded, placebo-controlled, parallel-group, randomised controlled trials: PROSPECTOR-1 is an Australian external pilot study for a future definitive, international, Phase III trial, PROSPECTOR-2.

### Methods: participants, interventions and outcomes

The study design for PROSPECTOR-1 and PROSPECTOR-2 is outlined in figure 1.

**Figure 1 F1:**
[figure not shown]
Study design for PROSPECTOR-1 (**PRO**longed versus **S**ingle dose in **PE**nicillin oral **C**hallenge **T**esting double-blind parallel-group randomised placebo-c**O**ntrolled t**R**ial) and PROSPECTOR-2 studies. ^a^penicillin ‘unspecified’, penicillin VK, penicillin G, amoxicillin, ampicillin, flucloxacillin, dicloxacillin, cloxacillin, mecillinam, pivmecillinam and pivampicillin. BID, two times a day.

#### Study setting

PROSPECTOR-1 will be undertaken at four tertiary hospital centres in Australia, including Austin Health (Victoria), Peter MacCallum Cancer Centre (Victoria), St George Hospital (New South Wales) and Royal Brisbane and Women’s Hospital (Queensland). PROSPECTOR-2 will be expanded to 14 tertiary hospital centres across Australia, Asia, North America, Africa and Europe (a complete list may be viewed in online supplemental table 1).

#### Eligibility criteria

Adult patients referred to inpatient or outpatient allergy services for a suspected immune-mediated penicillin allergy with a history of delayed or unknown timing will be eligible for inclusion in the study. Participants will then be risk-assessed using the PEN-FAST tool^37^ and RegiSCAR score. Participants will receive a single dose of 250–500 mg (PROSPECTOR-1) or 500 mg (PROSPECTOR-2) amoxicillin challenge (with or without prior skin testing). Participants who pass this initial challenge without an observed immune-mediated adverse event (1–2 hours post dose) will proceed to randomisation. The inclusion and exclusion criteria are listed in box 1.

Box 1Inclusion and exclusion criteriaInclusion criteriaAdult patients referred to the inpatient or outpatient allergy services for a suspected penicillin allergy with an immune-related allergy history of delayed (>6 hours after first dose of drug administration) or unknown timing, who tolerate the first single dose of an oral amoxicillin challenge.Willing and able to give consent and undergo telehealth/telephone review.Exclusion criteriaThe patient’s age is <18 years.Any other illness that, in the investigator’s judgement, will substantially increase the risk associated with the subject’s participation in this study.Stevens-Johnson syndrome or toxic epidermal necrolysis to beta-lactam.Inpatients concurrently receiving or likely to receive a beta-lactam antibiotic therapy during the 14-day study period.The concurrent use of antihistamines and systemic steroid therapy (ie, >10 mg daily) (PROSPECTOR-2).

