### Interventions

#### Intervention

Participants randomised to the intervention arm will receive a prolonged, 5-day course of oral 500 mg amoxicillin, administered two times a day, to commence the day following the initial single-dose amoxicillin oral challenge.

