#### Control

Participants randomised to the control arm will receive a prolonged, 5-day course of oral placebo (microcrystalline cellulose (MCC), prepared to be visually identical to the intervention, administered two times a day, to commence the day following the initial single-dose amoxicillin oral challenge).

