#### PROSPECTOR-2

The proportion of positive oral challenges (ie, immune-mediated reaction up to and including day 7 following the first test dose, as adjudged by an independent blinded panel), n (%). Subgroup analyses for the following parameters: admission setting (inpatient vs outpatient), index reaction phenotype—delayed versus unknown timing, risk (PEN-FAST score 0 vs 1–2 vs ≥3), immunocompromised status, sex, region (Australia vs Europe vs Asia vs North America vs Africa), clinic type (specialised allergy clinic vs non-allergy clinic), index reaction severity (RegiSCAR <2 vs ≥2), index reaction phenotype—severe MPE (RegiSCAR score 1 or 2) versus RegiSCAR score <1 versus RegiSCAR score >2 and index reaction timing—delayed exanthema <5 years post index reaction versus delayed exanthema >5 years post index reaction.

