### Participant timeline

The participant timeline is outlined in a schedule of enrolment, interventions and assessments for both studies (online supplemental table 2). After randomisation on day 0, participants will be provided with the study medication and a telehealth review will be scheduled for days 1, 5, 7 and 14 by a specialist allergy healthcare provider (ie, board-certified allergist, clinical immunologist and other clinicians with specialised training in allergy and immunology). If patients are inpatients at the time, then this review will be performed at the patient bedside. At each telehealth review, compliance will be recorded by reporting the number of doses taken, and participants will be asked about any other concurrent antibiotic therapy. If a positive oral challenge is reported, a summary of the patient-reported symptoms using a standardised questionnaire and clinical photography of any rash, cutaneous or mucosal changes will be sent to an independent review panel consisting of an allergist and dermatologist blinded to the intervention to ascertain if the reported reaction is an ‘immune-mediated adverse drug reaction’.

At days 30 and 90 post-randomisation, a telephone questionnaire and assessment of the medical record will be undertaken to assess for secondary outcomes including antibiotic-associated diarrhoea, *Clostridioides difficile* infection or acquisition of a multidrug-resistant organism. Patients at the day 90 follow-up will be unblinded if preferred by the site principal investigator, and those in the control arm will be offered a prolonged oral challenge.

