### Sample size

PROSPECTOR-1: A total of 120 participants are planned for inclusion (60 per arm). This sample size was chosen to provide a precise estimate of feasibility outcomes with a width of CI being <20% for any proportion. Such a sample size would also likely provide a reliable estimate of effectiveness as it has been shown that with binary outcomes, gain in precision is smaller once each group reaches 60 participants.^38^ This sample size also likely represents >9% of the definitive trial’s sample size (to detect a 5% difference assuming 8% event rate with 90% power and 5% significance level, a total of almost 900 participants would be required).^38^

PROSPECTOR-2: A total of 830 participants are planned for inclusion (415 per arm). The incidence of delayed reactions after single-dose oral challenge in the current literature is approximately 3%,^20^ while the incidence of delayed reactions after prolonged oral challenge is approximately 8%.^27 39^ To detect a 5% difference with 85% power and 5% significance level, 372 participants would need to be randomised to each arm. To account for a 10% loss to follow-up, a total of 830 participants will be recruited.

As the stipulated 5% difference reported in the literature and observed in our pilot data is not regarded as clinically relevant by many drug allergy specialists, we will also evaluate the non-inferiority of single-dose challenge. Given the lesser severity of an adverse event, a clinically relevant non-inferiority margin was determined to be 10% among investigators of this study. The planned sample size will enable us to evaluate a non-inferiority of the risk difference between study arms (secondary outcome) with double-sided 95% CI with 82% power (assuming real difference between arms being 5%).^40^ The sample size for PROSPECTOR-2 will be updated prior to study start based on the estimates observed in PROSPECTOR-1.

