### Recruitment

Recruitment will be undertaken by appropriately trained and delegated study investigators at participating sites in both the ambulatory clinic and inpatient settings. The central study team will monitor and encourage recruitment by regularly engaging with participating site staff, providing strategies for boosting enrolment and troubleshooting solutions. Recruitment number updates will be communicated through a regular study newsletter.

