### Methods: assignment of interventions

#### Allocation

Permuted block design randomisation will be used, stratified by the hospital site and setting (inpatient vs outpatient). While block design might result in larger treatment imbalances, such design is preferred to overcome logistical difficulties. Randomisation will be performed by the unblinded pharmacy dispensing team via REDCap just before the intervention. The allocation sequence will be concealed until the time of the randomisation.

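### The beta-lactam exclusion in Box 1 covers inpatients only, so an outpatient already on or expecting a beta-lactam can be randomised to placebo

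*Protocol article*

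**What the plan says.** The protocol article (Eligibility criteria, Box 1) lists among its exclusions "Inpatients concurrently receiving or likely to receive a beta-lactam antibiotic therapy during the 14-day study period". The sentence is confined to one setting.

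The trial is not. Box 1 admits adults referred to either inpatient or outpatient allergy services. The Recruitment section says that enrolment takes place "in both the ambulatory clinic and inpatient settings". The Allocation section has randomisation "stratified by the hospital site and setting (inpatient vs outpatient").

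The contrast under test is set out under Interventions. After one amoxicillin dose common to both arms, "Participants randomised to the intervention arm will receive a prolonged, 5-day course of oral 500 mg amoxicillin", while "Participants randomised to the control arm will receive a prolonged, 5-day course of oral placebo". The PROSPECTOR-2 primary outcome is the proportion of positive challenges, defined as an "immune-mediated reaction up to and including day 7 following the first test dose" and judged by a blinded panel.

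Outside antibiotic use is recorded during follow-up: at each review "participants will be asked about any other concurrent antibiotic therapy" (Participant timeline). Under Statistical methods, the primary analysis is by intention to treat and is repeated in a per-protocol population.

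**The concern.** By writing the exclusion at all, the authors accept that outside beta-lactam use during the study window matters. Limiting it to inpatients leaves the other recruitment setting open, and the article gives no reason for the difference. The remaining Box 1 exclusions (age, other illness raising risk, severe cutaneous reactions to beta-lactams, antihistamines and systemic steroids) do not address it.

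What is at stake is the separation between the arms. A control who takes a penicillin in the first week receives some of the repeated exposure that defines the intervention. Under intention to treat that person stays in the control arm, and the control event rate moves towards the intervention rate. This costs some power for superiority. It also makes non-inferiority of the single dose easier to declare, and for that claim the error runs in the unsafe direction.

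**Working it through.** **1. Does any other text close the gap?** Set side by side: the exclusion names inpatients; eligibility, recruitment and stratification all name both settings; no other exclusion reaches an outpatient on a beta-lactam. The question about concurrent antibiotics is asked at reviews after randomisation, so it records use but does not govern entry. The gap is there on the text.

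**2. Reproduce the plan's own figure.** Inputs from the Sample size section: control rate p0 = 3%, intervention rate p1 = 8%, 85% power, 5% significance (two-sided), 372 per arm, 10% loss to follow-up, 830 in total. With p̄ = (p0 + p1)/2 = 0.055,

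n = [1.960·√(2p̄(1 − p̄)) + 1.036·√(p0(1 − p0) + p1(1 − p1))]² / (p1 − p0)² = 371.8, rounded up to **372 per arm**.

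This matches exactly. Power at 372 per arm is 85.0%. Allowing for loss, 372/0.9 rounds up to 414 per arm, or 828 in total, against the 830 stated.

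**3. Dilute the control arm.** Let c be the share of all controls with relevant outside exposure before day 7, and e their excess risk over 3%. The control rate becomes 0.03 + c·e. Neither c nor e is given in the article; both are assumptions. Taking e = 5 points (affected controls react at the full 8%) is an upper bound. Taking e = 2.5 points halves the excess.

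Superiority power at 372 per arm:

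| c | Control rate, e = 5 | Power | Control rate, e = 2.5 | Power |
|---|---|---|---|---|
| 0% | 3.00% | 85.0% | 3.00% | 85.0% |
| 1% | 3.05% | 84.2% | 3.025% | 84.6% |
| 2% | 3.10% | 83.3% | 3.05% | 84.2% |
| 5% | 3.25% | 80.4% | 3.125% | 82.8% |
| 10% | 3.50% | 75.2% | 3.25% | 80.4% |

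**4. Effect on the secondary non-inferiority claim.** The margin is 10 points and the assumed true difference 5 points (Sample size section). With an unpooled standard error, power = Φ[(0.10 − (p1 − p0))/SE − 1.960], where SE = √[(p0(1 − p0) + p1(1 − p1))/372]. At e = 5 this gives 85.3% with no dilution, then 85.8%, 86.3%, 87.8% and 89.9% for c = 1%, 2%, 5% and 10%. The article states 82%, which this approximation does not reproduce, so only the direction and size of the change should be read from it.

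**The case against.** The case that this is minor is strong, and most of it stands.

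- **Equivalence.** A reader might infer that any control who takes a beta-lactam has in effect had a prolonged challenge. The article does not support that. The intervention is a 5-day amoxicillin course and the target is penicillin allergy; beta-lactam is a wider class, and nothing says that another agent or a shorter course produces the 8% rate.
- **Timing.** The exclusion spans 14 days but the primary endpoint closes at day 7. Use that starts after day 7 cannot affect it, and use that starts late in the first week leaves little time for a delayed reaction.
- **Frequency.** No share of affected controls is given, nor the inpatient/outpatient mix. People referred for suspected penicillin allergy seem unlikely to be taking a penicillin routinely. The 75.2% figure needs one control in ten exposed early at the full rate, and nothing in the article points to that.
- **Handling in the analysis.** A reader might also infer that the antibiotic data will go unused. The article promises a detailed statistical analysis plan, not shown here, and a per-protocol analysis. How outside antibiotics enter either is properly left there and is no fault of this document.
- **Misattributed reactions.** A reaction to an outside drug could be counted as a positive challenge, but this can occur in either blinded arm, and a blinded panel adjudicates. It is not shown to favour one arm.
- **Reach of the remedy.** Widening the criterion screens out only current or foreseeable use, so the power losses above would not all be recovered.

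These points limit the size of the problem. They do not explain why the criterion stops at inpatients, and an analysis plan cannot change who may enter.

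**Conclusion.** The point holds as a gap in the eligibility wording, with a consequence of unknown and probably small size. If 1% or 2% of controls are affected, superiority power falls by less than 2 percentage points even at the upper-bound reaction rate; at 5% it falls to 80.4%, or to 82.8% with half the excess risk. These figures rest on the plan's 3% and 8% rates, on 372 evaluable participants per arm, and on assumed shares of controls with relevant exposure before day 7.

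Direction matters more than size here. Dilution is conservative for the primary superiority question but anti-conservative for non-inferiority of the single dose. The stated sample size of 372 per arm and 830 in total is unaffected, and the documents do not support a claim that the trial is seriously biased or underpowered on this account.

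**What to change.** Apply the existing beta-lactam exclusion to all participants regardless of setting, or reconcile Box 1 with the recruitment and stratification text by stating why outpatients are exempt.

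The cost is a change of wording and a few outpatients who become ineligible. Prescriptions that nobody could foresee at randomisation will still occur.

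If participants with outside beta-lactam use before day 7 are examined separately, label that analysis supportive only. It conditions on something that happens after randomisation: a participant who has reacted may then be less likely to be given a beta-lactam, so dropping users can itself bias the comparison. The intention-to-treat analysis should stay primary.
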